## 1. Background

Cancer mortality has decreased significantly over the last years due to the earlier diagnosis and increasing efficiency of chemotherapy. The benefits of administering anti-cancer drugs are to some extend limited by their adverse effects on the cardiovascular system [1–4]. The most serious cardiotoxic effect of chemotherapy is damage to the heart muscle, leading to heart failure. Cardiotoxicity is particularly important in the context of anthracycline use. The main mechanism of anthracycline cardiotoxicity is direct myocardial cell damage [5–9].

In addition, studies have shown that oncological treatment, including anthracyclines, accelerates the development of atherosclerosis and its complications [1–4]. The mechanisms by which chemotherapy with anthracyclines may causes or promote premature atherosclerosis are multifactorial. Both endothelial damage as well as arterial thrombosis, microcirculation damage and long-term changes in lipid metabolism have been reported [10–13]. However, the impact of asymptomatic atherosclerotic lesions on the occurrence of heart muscle damage in the course of chemotherapy is still an open question and currently CT angiography or CAC scoring is not routinely performed.

Risk factors for cardiotoxicity include older age, arterial hypertension, diabetes, dyslipidemia, obesity and smoking, and they coincide with atherosclerosis risk factors [1]. Several, mainly retrospective, studies with statins in the prevention of heart failure have been published, but the mechanism of their cardioprotective effect is still unknown [14–23].

Studies that define the contribution of pre-existing coronary atherosclerosis and/or its progression to toxicity during anthracycline treatment are lacking. We therefore designed our study to define both cardiac function, by echocardiogram, and coronary atherosclerosis and calcification by CCTA, at baseline and at intervals in a cohort receiving anthracycline chemotherapy.

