## 2. Methods

### 2.1 Study structure

The ANTEC Trial is a single-center, prospective, observational trial evaluating the impact of atherosclerosis in the coronary arteries determined by computed tomography on the risk of cardiotoxicity related to anthracycline-based chemotherapy. The trial is being carried out in accordance with the principles of the Declaration of Helsinki and the International Conference on Harmonization Good Clinical Practice guidelines. The conduct of the study is approved by an Independent Ethics Committee at the Maria Sklodowska-Curie National Research Institute of Oncology in Warsaw (the date of approval– 28 October 2021, approval no. 80/2021) and all participants will provide written informed consent before study entry. The registration identifier on clinicaltrials.gov is NCT05118178.

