### 2.2 Study patients

The study will include patients with cancer, diagnosed and qualified for further systemic treatment with high-dose anthracycline chemotherapy at the Maria Sklodowska-Curie National Research Institute of Oncology in Warsaw. Patients must give informed and voluntary consent to participate in the study and meet all the inclusion criteria and none of the exclusion criteria listed in Table 1.

**Table 1 pone.0288146.t001:** Inclusion and exclusion criteria.

Inclusion criteria
1. Eastern Cooperative Oncology Group (ECOG) performance status from 0 to 2.
2. Age ≥18 years at the time of signing the informed consent.
3. Known neoplastic disease prior to the initiation of chemotherapy with a high dose of anthracyclines (doxorubicin ≥ 240 mg / m2 b.w. or epirubicin ≥ 600 mg / m2 b.w.)
4. No history of heart failure (left ventricular ejection fraction ≥ 50% as assessed by echocardiography).
5. No history of: coronary artery disease, stroke and lower limb atherosclerosis
6. At least moderate baseline cardiovascular toxicity risk according to Heart Failure Association–International Cardio-Oncology Society stratification [1]
Exclusion criteria
1. History of heart failure and/or left ventricle ejection fraction <50%
2. Significant valvular heart disease
3. Previous chemotherapy or radiation to the chest
4. Presence of any disease with a life expectancy <1 year in the opinion of the investigator.
5. Drug or alcohol abuse
6. Lack of possibility or contraindications for computed tomography (CT) scan.

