### 3.2 Sample size calculations and statistical analysis

The estimated group size was determined for the one-sided Pearson chi-square test for two proportions. We considered an alternative hypothesis of an approximately 2-fold increase in the incidence of cardiotoxicity with the presence of atherosclerotic lesions versus null hypothesis of no effect of atherosclerotic lesions. In particular, we assumed that the incidence of cardiotoxicity in the population with and without atherosclerotic lesions will vary from 60% to 75% and from 30% to 40% respectively and that the atherosclerotic lesions of various severity will be present in 30% to 40% of patients. With additional standard assumptions of 0.05 statistical significance and 80% power and assuming the estimated sample size varies from 54 to 80 individuals, thus the desired sample size of 80 was established.

Handling of missing data will depend on the proportion of cases affected by missing values. Complete case analysis will be performed if any missing values occur in less than 5% of cases. Otherwise, imputation through full conditional specification (FCS) methods are planned, accounting for the model of interest.

Statistical analysis of the results obtained in this trial will focus on the comparison of groups determined on the basis of the presence of atherosclerotic lesions, and will include a comparison of the characteristics of these groups using for comparisons of numerical variables, the Wilcoxon test, and for categorical variables the Fisher or chi-square tests. The Cochran-Armitage test on the existence of a trend for an ordinal scale variable will be used to assess the effect of the severity of atherosclerotic lesions on the incidence of cardiotoxicity.

Cumulative incidence of cancer therapy-related cardiovascular toxicity (primary endpoint) will be estimated using competing risk approach with death from other causes as the competing event. Fine and Gray’s proportional subhazards model will be used to estimate incidence by group and evaluate the impact of atherosclerotic lesions controlling for potential confounders. This model may be used in combination with missing data imputation, if necessary, with substantive model compatible fully conditional specification (SMC-FCS) imputation [24].

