For time-to-event secondary endpoint (all-cause mortality) we will use the Kaplan-Meier estimates with Long-rank test to compare the survival curves. In addition, cox proportional hazard model will be used for multivariate analysis if sufficient number of events is observed. Changes in numerical variables (ejection fraction, biomarkers’ concentration) by atherosclerotic lesions status will be investigated by two-way repeated measures ANOVA.

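### The ejection fraction and biomarker comparisons by lesion status use a two-way repeated measures ANOVA with no covariates, so a risk-factor effect on the change itself would be credited to lesions

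*Protocol article*

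**What the plan says.** All references are to the Protocol article.

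- **Design (Section 2.1):** "The ANTEC Trial is a single-center, prospective, observational trial evaluating the impact of atherosclerosis in the coronary arteries". Lesion status is observed on the baseline CT, not assigned.
- **Shared causes (Section 1):** "Risk factors for cardiotoxicity include older age, arterial hypertension, diabetes, dyslipidemia, obesity and smoking, and they coincide with atherosclerosis risk factors".
- **Primary endpoint (Section 3.2):** a Fine and Gray model is to "evaluate the impact of atherosclerotic lesions controlling for potential confounders".
- **Change endpoints (Section 3.2):** changes in numerical variables, with ejection fraction and biomarker concentrations as the examples, "by atherosclerotic lesions status will be investigated by two-way repeated measures ANOVA". No covariate is named.
- **Mortality (Section 3.2):** "For time-to-event secondary endpoint (all-cause mortality) we will use the Kaplan-Meier estimates with Long-rank test to compare the survival curves". In addition, a "cox proportional hazard model will be used for multivariate analysis if sufficient number of events is observed".
- **Limitations (Section 4.1):** confounding by other cardiotoxicity risk factors is acknowledged, and adjustment is promised in the multivariate analysis where feasible.
- **Data (Section 2.3, Tables 1 and 2):** age and the cardiovascular risk factors are recorded at baseline. The HFA-ICOS risk level is assessed for eligibility. Echocardiography is done at visits 1 to 5, and IL-6, MPO and TNF-alpha are measured at visits 1, 3 and 5.

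**The concern.** The protocol recognises confounding and adjusts for it in the primary model. It then names, for the change endpoints, a method whose only terms are lesion status and time.

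Patients with lesions can be expected to be older and to carry more of the risk factors listed in Section 1. Suppose older patients lose more ejection fraction under anthracyclines whatever their coronary status. The lesion-by-time contrast would then show a difference that lesions did not cause.

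This matters because Section 1.1 includes the influence of atherosclerosis on prognosis among the aims, and Section 4 suggests that the results may help identify patients who could benefit from preventive statins. Percentage fall in ejection fraction and GLS, and change in biomarkers, are listed secondary endpoints (Section 2.4.2).

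**Working it through.** **Plan's own figure.** The documents give no figure for these secondary comparisons. The only figure needed is the sample size, and it reproduces. A one-sided Pearson test at 0.05 with 80% power, 60% v 30%, lesions in 30% of patients, pooled variance and no continuity correction gives 24 + 56 = 80. With lesions in 30% to 40% of 80 patients, the groups run from 24 v 56 to 32 v 48.

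**Which differences bias the ANOVA.** Let a patient's change be Δ = a + b·age + error, with no lesion effect, and let lesion patients be d years older on average. The expected difference in mean change between groups is b·d. An age effect on the level that is the same at every visit drops out of Δ. Only an effect on the change (b ≠ 0) biases the group-by-time contrast.

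**Rejection rate for a given bias.** Take two time points, a two-sided 5% test and a bias of δ SD of the change. The noncentrality is λ = δ / √(1/n1 + 1/n2), and the rejection rate is 1 − Φ(1.96 − λ) + Φ(−1.96 − λ). The δ values are assumed.

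| Groups | √(1/n1 + 1/n2) | δ = 0.2 | δ = 0.4 |
|---|---|---|---|
| 24 v 56 | 0.244 | λ = 0.82, 13.0% | λ = 1.64, 37.4% |
| 32 v 48 | 0.228 | λ = 0.88, 14.2% | λ = 1.75, 41.8% |

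**What would produce such a bias.** A simulation took 80 patients with 35% having lesions (28 v 52), no lesion effect, age SD 10 years within group and residual SD 6 points for ejection fraction change, with 8,000 runs per cell. All inputs except the 80 and the 35%, which lies within the stated 30% to 40%, are assumptions.

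| Age gap | 1 point per 10 y | 2 points per 10 y | 3 points per 10 y |
|---|---|---|---|
| 0 years | 4.9% | 5.0% | 5.2% |
| 5 years | 6.5% | 10.5% | 14.6% |
| 10 years | 11% | 26% | 47% |
| 15 years | 19% | 51% | 80% |

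The two calculations agree. At a 10-year gap and 2 points per 10 years, the bias is 2 points and the within-group SD is √(36 + 4) = 6.32, so δ = 0.32. For 28 v 52, λ = 0.316/0.234 = 1.35, which gives 27% against 26% simulated. Slopes of 1 and 3 points at the same gap give δ = 0.16 and 0.45, so the assumed 0.2 to 0.4 lies between them.

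**With age in the model,** the rejection rate is 4.7% to 5.3% in every cell.

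**Mortality.** No death rate is given. An assumed 5% to 20% over 12 months gives 4 to 16 deaths among 80. At the customary 10 events per parameter, that supports 0.4 to 1.6 parameters, fewer than the two needed for lesion status and one confounder. Detecting a hazard ratio of 2 with 80% power (two-sided 5%, 30% to 40% with lesions) would need 69 to 78 deaths.

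**The case against.** - **Confounding is disclosed.** Section 4.1 names it and promises adjustment where feasible, without limiting this to the primary endpoint. That stands as evidence of awareness. It is conditional, however, and refers to a multivariate analysis, whereas the method named for the change endpoints is a two-factor ANOVA.
- **An article condenses.** Covariate lists and event thresholds are commonly left to the full protocol or analysis plan, and their absence is not criticised here. The point concerns the method that is named. If the full plan already adds covariates, only the wording needs changing.
- **A prognostic aim needs no adjustment.** If lesion patients do worse because they are older, an unadjusted test is right to reject equality, and a false positive exists only under a reading about the effect of lesions. This limits the point. It does not remove it, because the protocol also speaks of impact and influence and adjusts its own primary model.
- **Repeated measures remove baseline differences.** True for stable differences in level, not for effects on the change. Section 1 makes such an effect plausible for ejection fraction, since it lists age as a cardiotoxicity risk factor. It says nothing about IL-6, MPO or TNF-alpha, so the case there is weaker.

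A reader might also infer that the mortality analysis is defective because adjustment disappears just when deaths are few, so that age alone could produce an apparent lesion effect. The documents do not support this. An adjusted Cox model is planned, and withholding it when events are few is ordinary practice. The shared risk factors in Section 1 are those of cardiotoxicity, not of 12-month death. Neither a death rate nor an event threshold is stated, so it is inference that the log-rank test would stand alone. Fitting a penalised two-parameter model to a handful of deaths regardless would be a debatable choice.

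**Conclusion.** The point holds for the change endpoints. As written, the ANOVA cannot separate an effect of lesions on the change in ejection fraction from an effect of age or another shared risk factor on that change, and the conditional promise in Section 4.1 does not cure this.

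The size is illustrative. An assumed bias of 0.2 to 0.4 SD gives about 13% to 42% rejections against 5%. The documents give no age gap, age slope or SD of change. With a small gap and a shallow slope the inflation is slight (6.5%), and with no effect on the change there is none.

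For mortality, all that remains is a matter of interpretation: the plan should say how an unadjusted result will be read if the Cox model cannot be fitted. The adjusted primary analysis is not affected.

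**What to change.** In Section 3.2, replace the two-way repeated measures ANOVA for ejection fraction, GLS and biomarkers with a repeated-measures mixed model. Its terms would be lesion status, time and their interaction, plus the baseline value, age and HFA-ICOS risk category, each with its interaction with time. The follow-up values should be the outcome (visits 2 to 5 for echocardiography, 3 and 5 for biomarkers). If visit 1 were kept among the outcomes, an age main effect alone would not remove the bias, because the age-by-time term does that work.

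For mortality, keep the conditional Cox model and add one sentence: if events are too few for it, the Kaplan-Meier and log-rank results are unadjusted and descriptive and will not be read as an effect of lesions.

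Cost: wording only, because every covariate is already obtained at visit 1. The model spends a few degrees of freedom, and intervals widen because age and lesion status are correlated. For age alone, with 35% lesions and age SD 10, the variance factor is 1 + 0.35 × 0.65 × (d/10)². That makes intervals about 3%, 11% and 23% wider at assumed gaps of 5, 10 and 15 years, before any gain from a smaller residual variance. Adjusting for the baseline value also answers a slightly different question from comparing raw changes when groups differ at baseline, so the text should name which estimate is reported.

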### 2.3 Study visits and follow up

Approximately 80 patients are planned to be included in the study. Each patient will have 5 program visits every 3 months for 12 months. At the first visit, the patient will be informed about the type of the proposed follow-up, its course and planned tests. After signing the consent to participate in the study, patients will undergo planned procedures according to the schedule shown in Table 2.

**Table 2 pone.0288146.t002:** Schedule of Activities (SoA).

Visit	1	2	3	4	5
Days from first Visit window	1	90 (±14)	180 (±14)	270 (±14)	360 (±14)
Informed Consent	x				
In-/exclusion criteria	X				
Medical History/ Concomitant diagnoses	x				
Demographics	x				
NYHA classification	X	X	X	X	X
ECOG performance status	X	X	X	X	X
Physical exam	X	X	X	X	X
Concomitant Therapy	X	X	X	X	X
Assessment of Endpoints		X	X	X	X
12-lead-ECG	X	X	x	X	x
Echocardiography with GLS assessment	x	X	X	X	X
Lab test	x	X	X	X	X
CCTA	x				
IL-6, MPO, TNF-alpha	x		x		x

**Abbreviations**: ECG = electrocardiogram; ECOG = Eastern Cooperative Oncology Group; GLS = global longitudinal strain; NYHA = New York Heart Association; CCTA = Coronary Computed Tomographic Angiography

Clinical variables such as: age, gender, cardiovascular risk factors (hypertension, diabetes, hyperlipidemia, obesity, smoking status), alcohol use, previous medical history, concomitant heart failure therapy, statins or other lipid lowering medications will be documented at baseline and then checked at each visit. Lipid levels and diabetes status at each visit will be determined using a fasting blood sample and lipid panel at that visit.

Cancer diagnosis and current treatment (including cumulative dose of anthracyclines) will be collected and documented at each visit.

In all patients, a single coronary computed tomographic angiography (CCTA) will be performed at the beginning of the study, with calculation of coronary artery calcium (CAC) score according to the Agatston method. Contrast cardiac CT scanning for CAC quantification will be performed with a 64-slice CT scanner (Revolution Evo, GE Healthcare, Waukesha, USA) with prospective ECG triggering. A tube voltage of 120kVp will be used. Images will be reconstructed with a slice thickness of 0.625 mm and CACS was quantified using the Agatston method with dedicated software by a well-trained researcher.

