At each visit, transthoracic echocardiography will be performed by using a Philips EPIQ Elite instrument (Philips Healthcare, Andover, Massachusetts). The following echocardiographic parameters will bez assessed: left atrium diameter, interventricular septum diameter, posterior wall thickness, left ventricle (LV) end-diastolic diameter, LV end-systolic diameter, LV ejection fraction, and mitral inflow with the use of Doppler echocardiography. Diastolic function will be evaluated by mitral inflow E/A pattern, E/A ratio, annular tissue Doppler curves and E/E’ ratio. Images will be digitally stored for offline analysis on custom software (Q-Station, Philips Healthcare, Andover, Massachusetts). Left ventricular, two-dimensional peak systolic global longitudinal strain (GLS) will be analysed by an offline semi-automated speckle tracking imaging technique from the three standard apical views. Analyses will be performed by one board-certified physician, who will be blinded to all clinical characteristics.

Blood samples will be collected et each visit and analyzed by the central laboratory (The Maria Sklodowska-Curie National Research Institute of Oncology). Laboratory tests will include: alkaline phosphatase, alanine aminotransferase (ALT), aspartate aminotransferase (AST), urea, creatinine, glucose, magnesium, potassium, sodium, uric acid, morphology, glycated hemoglobin, lipid profile, d-dimers, fibrinogen and hs-CRP.

Blood samples to determine plasma levels of high-sensitivity troponin T (hs-cTnT) and N-terminal natriuretic pro-peptide (NTproBNP) will be processed in a central laboratory using standardized methods. New atherosclerosis biomarkers (IL-6, MPO, TNF-alpha) will be assessed every 6 months using Quantikine ELISA kit R&D Systems, Inc., USA & Canada.

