#### 2.4.2 Secondary endpoints

The secondary composite endpoint include: time to all-cause death, cardiovascular death, myocardial infarction, and stroke.

Other secondary endpoints include: (1) the severity of atherosclerosis in the coronary arteries and the calcification index in computed tomography, (2) the percentage decrease in left ventricular ejection fraction and GLS in echocardiography, (3) changes in the concentration of biomarkers involved in inflammatory and atherosclerotic processes.

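### Repeated-measures ANOVA for ejection fraction and biomarkers forces deletion or outcome imputation of incomplete patients; a linear mixed model with a stated rule for death fits the data better, for a modest gain

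*Protocol article*

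**What the plan says.** Section 2.3 sets the measurement times: "Each patient will have 5 program visits every 3 months for 12 months". Table 2 places echocardiography with GLS at all five. For the cytokines, "New atherosclerosis biomarkers (IL-6, MPO, TNF-alpha) will be assessed every 6 months", which Table 2 shows as visits 1, 3 and 5.

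Section 2.4.2 lists among the secondary endpoints "the percentage decrease in left ventricular ejection fraction and GLS in echocardiography" and changes in biomarker concentrations.

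Section 3.2 fixes the analysis: changes in numerical variables, with ejection fraction and biomarker concentration named in brackets, "by atherosclerotic lesions status will be investigated by two-way repeated measures ANOVA".

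Section 3.2 also gives one general rule for missing data: "Complete case analysis will be performed if any missing values occur in less than 5% of cases". It continues: "Otherwise, imputation through full conditional specification (FCS) methods are planned, accounting for the model of interest". Death is mentioned in the analysis of the primary endpoint, as a "competing risk approach with death from other causes as the competing event". The article does not say how ejection fraction or biomarker values after death are treated in the ANOVA.

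**The concern.** Classical repeated-measures ANOVA cannot use a partly observed patient. Someone with four of five echocardiograms must be removed or completed, so the choice of method creates a missing-data step that these data do not otherwise require. It also assumes sphericity across five time points, and correlations that weaken as visits move apart break that assumption.

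Cancer patients followed for a year during and after chemotherapy will miss some visits, and some may die. The plan itself expects deaths: all-cause death is part of the secondary composite, and death from other causes is a competing event for the primary endpoint. The general missing-data rule nevertheless makes no exception for a value that is absent because the patient has died. The lesion-by-time comparison behind the echocardiographic and biomarker secondary endpoints would then depend on how an unstated case is resolved.

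**Working it through.** **The plan's own figure.** The article gives no sample size, power or standard deviation for the repeated-measures analysis. Its N of 80 for the primary endpoint does reproduce. Take 60% against 30%, lesion prevalence 30%, k = 0.7/0.3, pooled proportion 0.39, one-sided alpha 0.05 and power 80%. Then n1 = [1.645·√(0.39·0.61·(1+1/k)) + 0.842·√(0.6·0.4 + 0.3·0.7/k)]² / 0.3² = 23.1, rounded up to 24. With 24·k = 56 in the other group, the total is 80. Here N serves only as the denominator.

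**How many patients can be deleted.** I read cases as patients. 5% of 80 is 4, and the rule requires less than 5%, so at most 3 patients (3/80 = 3.75%) can be dropped. A fourth incomplete patient (4/80 = 5.0%) moves the analysis to imputation. This step needs no assumed miss rate.

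**What miss rate triggers imputation.** The documents give no miss rate, so m per follow-up visit is an assumption, taken as equal and independent across visits, with baseline complete.

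- Echocardiography, four follow-up visits: 1 − (1 − m)⁴ = 0.05 gives m = 1 − 0.95^(1/4) = 1.3%.
- Cytokines, two follow-up draws: 1 − (1 − m)² = 0.05 gives m = 1 − 0.95^(1/2) = 2.5%.

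| m per visit | EF incomplete | EF complete, of 80 | Cytokines incomplete | Cytokines complete, of 80 |
|---|---|---|---|---|
| 1.25% | 4.9% | 76.1 | 2.5% | 78.0 |
| 2% | 7.8% | 73.8 | 4.0% | 76.8 |
| 3% | 11.5% | 70.8 | 5.9% | 75.3 |
| 5% | 18.5% | 65.2 | 9.8% | 72.2 |
| 10% | 34.4% | 52.5 | 19.0% | 64.8 |

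The complete-patient columns show how far the threshold is passed. They do not show how many patients the plan would lose, since above 5% it imputes. If misses cluster in the same patients, fewer are incomplete at a given m.

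**How large the gain could be.** A simulation of 400 trials compared the group difference in 12-month EF change from complete cases with that from a likelihood fit with unstructured covariance. Assumed inputs: SD 6 points, correlation 0.6 between visits, 28 patients with and 52 without lesions, true difference −4 points.

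| Missingness (assumed) | Complete patients | Complete cases: mean (SD) | Likelihood fit: mean (SD) |
|---|---|---|---|
| 5% of visits at random | 65.1 | −3.97 (1.40) | −4.00 (1.30) |
| Lighter dropout depending on previous EF | 69.3 | −4.15 (1.40) | −4.13 (1.37) |
| Heavier dropout depending on previous EF | 60.3 | −3.93 (1.37) | −3.94 (1.33) |

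In the first row complete cases carry (1.40/1.30)² = 1.16 times the variance, 16% more. In the other two the ratio is (1.40/1.37)² = 1.04 and (1.37/1.33)² = 1.06. The two methods' means are almost the same in every row, so these settings show no bias of one relative to the other. The comparator is complete-case analysis, which the plan would not run at these rates, so 16% is not a loss under the plan.

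**Death.** Set side by side, 2.4.2 counts all-cause death, 3.2 treats death as competing for the primary endpoint, and the missing-data rule in 3.2 is general. Table 1 excludes "Presence of any disease with a life expectancy <1 year in the opinion of the investigator", which reduces deaths within 12 months but does not rule them out.

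**The case against.** The strongest reply is that the plan already deals with missing data. A reader might infer that the ANOVA drops every patient with a missed visit and so analyses only the healthiest survivors. The article does not support that: deletion is capped at 3 of 80 patients, and beyond that the plan imputes. Under missing at random, properly specified imputation gives roughly what a mixed model gives, so the choice between them is partly one of convenience. This stands, and it limits the size of the point.

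A reader might also infer that the plan will impute ejection fractions for dead patients. The article never says so. It follows only from a general rule with no exemption, and the fuller protocol or analysis plan may settle it. What stands is that the rule as worded allows it.

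Nor is the mixed model free, or a cure for death. It needs a covariance structure and missing at random, and leaving out rows after death does not by itself give a while-alive estimand, because the fit still borrows across patients as if trajectories continued.

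The smaller matters are weak alone. Sphericity corrections are routine. The article neither states nor excludes a transformation of the biomarkers. The bracket naming ejection fraction and biomarkers can be read as examples, so the absence of GLS may be only a wording gap.

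None of this defends the ANOVA itself. It is a stated choice, and it is the reason that partial rows must be deleted or filled in.

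**Conclusion.** The point holds as a worthwhile, inexpensive improvement to a method that the article fixes. Four incomplete patients of 80, or about 1.3% of follow-up echocardiograms missed per visit if misses are equal and independent, are enough to make outcome imputation necessary. A likelihood-based model would not need it. The treatment of values after death is open and should be closed.

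The consequence is limited. The analysis serves secondary endpoints only, the Fine and Gray analysis of the primary endpoint is untouched, and N stays at 80. No harm under the plan's actual rule has been quantified: the miss rates and simulation inputs are assumptions, and the simulated differences are against complete cases rather than imputation.

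**What to change.** In 3.2, replace the two-way repeated-measures ANOVA with a linear mixed model for repeated measures:

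- All observed visits, baseline included, are responses. Fixed effects are lesion group, visit and group-by-visit, with unstructured covariance and no imputation of the outcome.
- Apply it to LVEF, to GLS by name, since 2.4.2 lists it, and to the biomarkers, log-transformed if skewed.
- Report the group-by-visit contrasts with 95% confidence intervals.
- State that values after death are not imputed, and name the estimand (for example, change while alive). If that estimand needs more than the mixed model, such as a joint model with survival, say so.

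The cost is a few sentences and standard software, with no new data and no change in sample size. The price in assumptions is missing at random and a covariance choice. Unstructured covariance means 5·6/2 = 15 parameters for the echocardiographic measures and 3·4/2 = 6 for the cytokines, so a simpler fallback structure should be named in case the fit does not converge.
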